### Hypotheses

We hypothesize that (1) both therapeutic programs will have a greater clinical impact on the reduction of anxiety symptoms, perceived stress, and depressive symptoms compared with a WLC in the short term (2 months), and this effect will be maintained in the long term (6 months); (2) the 2 therapeutic programs will have the same effectiveness in reducing these symptoms; (3) both therapies will be more cost effective than will WLC; (4) these 2 programs both reduce the consumption of tobacco, alcohol, and drugs compared with WLC; and (5) participants will be satisfied with the 2 therapeutic programs.

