#### Secondary Objectives

For the secondary endpoints of the HADS anxiety subscale, PSWQ, VAS-stress, PSS, BDI, and HADS depression subscale scores, comparisons of the changes between the baseline and the 2-month visit between each experimental group and the control group will be performed separately with the same methodology used for the primary endpoint.

Comparison of the change between the baseline and the 6-month visit for the primary endpoint and secondary endpoints between each experimental group and the control group will be performed separately using a linear mixed model. In this model, we will include the 2 measurements (at 2 and 6 months) for the time effect, the group effect (experimental/control), an adjustment for baseline values and center, and a time × group interaction. A contrast with a 2.5% type I error will be used to compare the 6-month change between the experimental and the control group.

The efficacy of the 2 therapeutic programs (face-to-face versus digital support) at 2 and 6 months will be compared using an analysis of covariance at the 5% significance level to compare the variations in the STAI score between the groups, adjusting for the baseline value.

VAS satisfaction and consumption of tobacco, alcohol, and drug use will be analyzed in each group using descriptive statistics.

The full version of the protocol can be viewed in Multimedia Appendix 4.

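### The aims call for comparing the two programs on stress, worry, anxiety and depression, but the article specifies that comparison for the STAI only

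*Protocol article*

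**What the plan says.** **Aims of the Study.** The second secondary objective is to compare change in stress, worry, anxiety and depressive symptoms in the two programs at 2 and 6 months.

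**Hypotheses.** The second hypothesis is that "the 2 therapeutic programs will have the same effectiveness in reducing these symptoms". The symptoms meant are those of the first hypothesis: anxiety, perceived stress and depression.

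**Statistical Analysis, Secondary Objectives.** Three comparisons are laid out:
- At 2 months: "For the secondary endpoints of the HADS anxiety subscale, PSWQ, VAS-stress, PSS, BDI, and HADS depression subscale scores", the comparison is made "between each experimental group and the control group will be performed separately with the same methodology used for the primary endpoint".
- At 6 months: the comparison is made "for the primary endpoint and secondary endpoints between each experimental group and the control group will be performed separately using a linear mixed model".
- Program against program: "The efficacy of the 2 therapeutic programs (face-to-face versus digital support) at 2 and 6 months will be compared" by analysis of covariance at the 5% level, "to compare the variations in the STAI score between the groups, adjusting for the baseline value".

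**The concern.** The between-program sentence does not leave the outcome open. It names one scale, the STAI, while the same section lists the six other scales and assigns them to comparisons with control. A SAP that followed this text would contain no direct estimate of digital versus face-to-face delivery for stress, worry or depression, although the aims ask for one.

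What would then be available on those domains is a pair of separate program-versus-control results for each scale. Setting them side by side, for instance one significant and one not, is not a valid comparison of the programs. Two significant results do not show that the programs are alike either. If between-program contrasts on these scales were added after the data had been seen, they would be post hoc.

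The mismatch is one of scope. It would exist whether the programs were compared by a test of difference or by an equivalence analysis.

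**Working it through.** **1. Objective against analysis.** The scales are grouped by domain as in Outcome Measures. Secondary Criteria gives 2 and 6 months for all of them.

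| Domain in the objective | Scales | Program vs control specified | Program vs program specified |
|---|---|---|---|
| Anxiety | STAI-T | yes | yes, 2 and 6 months |
| Anxiety | HADS anxiety | yes | no |
| Worry | PSWQ | yes | no |
| Stress | PSS, VAS-stress | yes | no |
| Depression | BDI, HADS depression | yes | no |

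By domain, 1 of 4 is covered (anxiety, through the STAI) and 3 of 4 are not. By scale, 1 of 7 is covered and 6 are not. By scale and visit, 7 × 2 = 14 cells, of which 1 × 2 = 2 are specified and 6 × 2 = 12 are not. The article does not state the figure 14; it comes from counting every named scale at both visits.

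**2. The plan's own sample size.** Sample Size gives a difference of 11.5, an SD of change of 14.6 (r = 0.5), two-sided α = 0.025 and power 80%.
- SD of change: √(2 × 14.6² × (1 − 0.5)) = 14.6, as stated.
- n per group: 31 by the normal approximation and 31.93 by the t-test, so 32, as stated.
- Allowing for 20% missing: 32 / 0.80 = 40 per group, 120 in total, as stated.

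The figure reproduces. It was set for each program against control, at a difference of 11.5 / 14.6 = 0.79 SD, and not for program against program.

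**3. Precision of a direct between-program estimate.** In SD units, the 95% half-width with n per arm is 1.96 × √(2/n). Baseline adjustment multiplies it by √(1 − r²). The article assumes r = 0.5 for the STAI; using it for the other scales is an assumption made here. √(1 − 0.25) = 0.866.

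| Per arm | Unadjusted | Adjusted, r = 0.5 |
|---|---|---|
| 40 (no loss) | 1.96 × √(2/40) = 0.44 SD | 0.44 × 0.866 = 0.38 SD |
| 32 (20% missing, as planned) | 1.96 × √(2/32) = 0.49 SD | 0.49 × 0.866 = 0.42 SD |

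For scale, the Introduction cites a meta-analysis of computer- and Internet-based interventions with effects of d = 0.32 (anxiety) to 0.43 (stress). A half-width of 0.38 to 0.49 SD is about as large as those whole effects.

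**4. Multiplicity if all cells were tested.** With independent tests at an unadjusted 5%, the chance of at least one false positive is 1 − 0.95¹⁴ = 51% for 14 tests, against 1 − 0.95² = 9.75% for the two specified. The scales are correlated, so 51% is an upper-end illustration. It is the reason to treat added contrasts as estimates and not as tests.

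**The case against.** **The objective can be read differently.** It speaks of change in the two programs, not between them, and neighboring objectives worded in a similar way are answered against control or descriptively. On that reading the program-versus-control analyses of the six scales serve it. The ambiguity is real, but the second hypothesis sets program against program and refers to stress and depression as well as anxiety. Even on the alternative reading, that hypothesis has no analysis for stress or depression; only worry, which it does not name, would drop out.

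**A reader might infer that 12 of 14 promised comparisons will never be made and that the objective cannot be answered.** The documents do not support this. The objective names four domains, not fourteen comparisons, and one of the four is covered by the STAI. The full protocol (an appendix to the article) and the SAP are not shown, so the most that can be said is that this article does not specify the comparisons. All three groups are assessed at each visit, so nothing prevents the analysis.

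**A reader might also infer that the added estimates would settle whether the programs are equally effective.** They would not: the intervals are about as wide as a whole treatment effect, and wider still once the planned 20% missing data is allowed for.

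**Limiting an unpowered comparison to the primary scale is defensible.** This stands as a design choice. The objective and hypothesis would then have to say so.

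**Conclusion.** The mismatch holds, in limited form. Read together, the objective and the second hypothesis call for a between-program comparison across the symptom domains, while the statistical section fixes that comparison to the STAI. As specified in this article, stress, worry and depression (three of four domains; six of seven scales when HADS anxiety is counted) have no between-program analysis at either visit. Because the section names the scale, this is a contradiction in the text and not a detail left to the SAP.

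It is worth correcting but moderate in weight. It concerns secondary outcomes only; the primary analysis and the sample size are untouched. The conclusion rests on reading the objective in the light of the second hypothesis, and on the article alone. The precision figures rest on 32 to 40 evaluable patients per arm and an assumed r = 0.5 on every scale.

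**What to change.** In Statistical Analysis, Secondary Objectives:
- Extend the face-to-face versus digital analysis of covariance to HADS anxiety, PSWQ, PSS, VAS-stress, BDI and HADS depression at 2 and 6 months.
- Fit it in a model that contains both program arms. The contrast cannot be taken from the models already planned, because each is fitted separately for one program and the control.
- Adjust for the baseline value of the scale and for center. Center is the randomization stratum and is in the other models, but the current between-program sentence omits it.
- Report each difference with its 95% confidence interval. Label the non-STAI contrasts as secondary estimates without confirmatory claims.
- State that neither a difference between the programs nor their sameness will be inferred from their separate results against control.

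Alternatively, if a STAI-only comparison was intended, narrow the secondary objective and the second hypothesis to the STAI.

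The cost of the first route is a short change to the text and twelve more secondary estimates to report, from data already being collected; no patients or visits are added. The second route costs only wording. Either can be done before the database is frozen, the point by which the article says the SAP will be validated.

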#### Assessments

Assessments are conducted for the 3 groups at baseline, 2 months, and 6 months. At baseline, participants complete the self-administered questionnaires for anxiety and depressive symptoms, and care contacts and medications are recorded. At 2 and 6 months, an evaluation of overall satisfaction as well as adverse events is additionally carried out. Self-assessments are collected in the face-to-face sessions with the investigator.

It is the same psychiatrist investigator for each site who generated the random allocation sequence, enrolled the participants, assigned the participants to the interventions, and assessed the participants, so he is not blinded to the intervention group.

The flowchart in Figure 1 summarizes the experimental design.

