#### Sample Size

In a study on the clinical and psychometric characteristics of ADA, the mean (standard deviation) of the STAI baseline score was 52.1 (SD 14.6) [4]. Two clinical studies with patients with generalized anxiety disorder, 1 comparing CBT with relaxation [61] and the other comparing CBT with brief psychodynamic psychotherapy [62], showed changes in the STAI-T scores of 7 and 16, respectively. In view of these results, we hypothesize that an average difference between each experimental arm and the control arm of 11.5 (the mean of 7 and 16). To demonstrate this difference in variation with a standard deviation of the STAI score change of 14.6 (assuming a conservative correlation coefficient of 0.5 between the baseline and 2-month STAI measures), a 2.5% type I error (using a Bonferroni correction for the 2 prespecified comparisons), and a power of 80%, it is necessary to include 32 patients per group. Although analysis of the primary outcome will be adjusted for baseline values, the sample size calculation does not take into account this adjustment to maximize the power. Finally, considering 20% ​​missing data, 120 patients (40 per group) are planned in this clinical trial.

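### Hypothesis 4 compares substance use with the wait list, but the plan only describes it within each group at 2 months and is ambiguous at 6 months; the article lists no outcome for the cost-effectiveness hypothesis

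*Protocol article*

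**What the plan says.** The Hypotheses section of the Protocol article words two of its five hypotheses as comparisons with the wait list control (WLC) on substance use and cost. Hypothesis 4 is that "these 2 programs both reduce the consumption of tobacco, alcohol, and drugs compared with WLC". Hypothesis 3 is that "both therapies will be more cost effective than will WLC".

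Consumption of tobacco, alcohol and drugs is a listed secondary outcome at 2 and 6 months, both in Aims of the Study and under Secondary Criteria, where the units are given: cigarettes per day, drinks per week, and days of use per week for each drug. The Assessments section adds: "Assessments are conducted for the 3 groups at baseline, 2 months, and 6 months".

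The Secondary Objectives part of Statistical Analysis then has three relevant sentences.

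- At 2 months, between-arm comparisons by the primary method are planned "For the secondary endpoints of the HADS anxiety subscale, PSWQ, VAS-stress, PSS, BDI, and HADS depression subscale scores".
- At 6 months, a linear mixed model with a 2.5% contrast is planned: "Comparison of the change between the baseline and the 6-month visit for the primary endpoint and secondary endpoints between each experimental group and the control". The secondary endpoints are not listed in that sentence.
- Last, "VAS satisfaction and consumption of tobacco, alcohol, and drug use will be analyzed in each group using descriptive statistics".

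On cost, neither outcome list contains a cost, utility or resource-use measure, no stated objective concerns cost, and no economic analysis is described. The nearest item is in Assessments, where at baseline "care contacts and medications are recorded".

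**The concern.** A hypothesis that names a comparator needs a contrast with that comparator. The plan chooses a method for consumption that yields three separate summaries and no difference between arms. This is not a detail left for the SAP, because the article itself fixes the descriptive analysis.

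The risk lies in what is written at the end. Consumption may fall in any arm as the disorder runs its course; the article's own definition of the disorder says symptoms generally abate within 6 months of the event. The WLC arm is there to separate that from an effect of the programs. Without a difference and its interval, a reader is left to compare three columns by eye, and a fall in the program arms may be reported as support for hypothesis 4 with no measure of its uncertainty.

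For hypothesis 3 the gap is earlier in the chain: the article states the hypothesis but lists nothing that could be used to test it.

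**Working it through.** **1. Hypotheses against planned analyses**

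| Item | Hypothesis | Listed as outcome | Analysis at 2 months | Analysis at 6 months |
|---|---|---|---|---|
| Anxiety, stress and depression scales | vs WLC | yes | between-arm ANCOVA | between-arm mixed model |
| Tobacco, alcohol, drugs | vs WLC (no. 4) | yes, 2 and 6 months | descriptive, per group | descriptive by the specific sentence; mixed model if the general sentence is read to include it |
| Cost effectiveness | vs WLC (no. 3) | not in this article | none | none |

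At 2 months the position is clear. The sentence names the HADS anxiety and depression subscales, PSWQ, VAS-stress, PSS and BDI, and consumption is absent. At 6 months there are two readings. If the later and more specific sentence governs, there is no contrast. If the general sentence governs, consumption has two different analyses, one of them a linear model of counts. Either way the text needs correcting.

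**2. The plan's own sample size, as a check on the inputs**

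Inputs from Sample Size: difference 11.5, SD 14.6, type I error 2.5% per comparison (taken as two-sided; the article does not say), power 80%, missing data 20%.

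- SD of change with correlation 0.5: √(2 × 14.6² × (1 − 0.5)) = 14.6, as stated.
- Normal approximation: n = 2 × (2.241 + 0.842)² × (14.6/11.5)² = 30.6, rounded up to 31.
- Noncentral t: power is 0.787 at 31 and 0.801 at 32, so 32 per group, as stated.
- 32/0.8 = 40 per group and 3 × 40 = 120, as stated.

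No stated number is in dispute.

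**3. What a between-arm comparison of consumption could show**

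The documents give no SD or expected effect for consumption, so these results are in SD units and assume a roughly normal outcome at two-sided 2.5%.

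Detectable difference at 80% power, normal approximation, (2.241 + 0.842) × √(2/n):

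- n = 40: 3.083 × 0.2236 = 0.69 SD (noncentral t: 0.70)
- n = 32: 3.083 × 0.25 = 0.77 SD (noncentral t: 0.79)

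Half-width of a 97.5% confidence interval, t × √(2/n):

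- n = 40: 2.285 × 0.2236 = 0.51 SD
- n = 32: 2.297 × 0.25 = 0.57 SD

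Power over an assumed true difference of 0.2 to 0.5 SD (normal approximation):

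- n = 40: about 9% to 50%
- n = 32: about 7% to 40%

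The 40-per-arm figures assume complete data; 32 is what remains after the planned 20% loss. Skewed counts with many non-users could behave differently, so these are a guide to the order of size only.

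**The case against.** Four points can be made for the plan.

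**Description may be a sensible choice.** Three substances, two programs and two visits make 3 × 2 × 2 = 12 contrasts, more if each drug is taken separately, and all would have low power. The matching secondary objective speaks only of measuring the programs' impact and names no comparator. This stands as an argument for labelling the contrasts secondary or exploratory, or for rewording the hypothesis. It does not justify keeping a comparative hypothesis with no contrast.

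**The control figures will be reported.** The descriptive analysis covers each group, WLC included, so a fall common to all arms would be visible. Patients are also selected on HADS scores, not on consumption, which weakens any appeal to regression to the mean. Both points stand. What is missing is the estimated difference and its interval.

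**The 6-month mixed model may cover consumption.** It may, on its wording, so one cannot say that no inferential contrast exists anywhere. But that reading collides with the descriptive sentence and leaves 2 months untouched.

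**The article condenses a fuller protocol.** It refers to the full version in Multimedia Appendix 4, which is not at hand and could hold an economic component. This stands, and it limits the point on hypothesis 3 to what the article lists.

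A reader might go further and infer that the trial cannot answer hypothesis 4, or that hypothesis 3 has no outcome at all. The documents support neither. Consumption is to be recorded at 2 and 6 months and all arms attend those visits, so only the planned analysis falls short. For hypothesis 3, one can say only that this article lists no outcome.

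**Conclusion.** The point holds in a limited form. For hypothesis 4, the analysis as written gives no between-arm estimate or interval at 2 months and an ambiguous one at 6 months, for a listed secondary outcome that the hypothesis itself compares with WLC. The contradiction is within the article and does not depend on any calculation.

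Its size is moderate. The primary endpoint, sample size and main inference are untouched. Adding the comparison would not make it a powerful test: under the assumptions above, only differences of roughly 0.7 to 0.8 SD would be reliably detected. The gain is an honest interval in place of an informal comparison of columns.

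For hypothesis 3, the conclusion is conditional: nothing listed in the article can test it, and that changes only if the full protocol contains an economic outcome and analysis.

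**What to change.** In Statistical Analysis, Secondary Objectives:

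- Replace the descriptive-only rule for consumption with an estimated difference between each program and WLC at 2 and 6 months, adjusted for baseline consumption and center. Use a model suited to skewed or zero-heavy counts, for example negative binomial or robust standard errors for cigarettes and drinks, and an ordinal or rank-based method for days of drug use. Report confidence intervals and label the results secondary or exploratory.
- List the endpoints covered by the 6-month linear mixed model and state that it does not apply to consumption.
- Keep satisfaction descriptive.
- If the comparison is not adopted, restate hypothesis 4 as descriptive and draw no comparative conclusion from it.

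For hypothesis 3, point to the economic outcome and analysis in the full protocol if they exist. Otherwise remove the hypothesis or state that this trial does not test it.

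The cost is a few extra models on data already planned, and some wording. The downside is a further set of low-powered secondary contrasts, which the labelling deals with. There is time: the article reports 50 of 120 patients included, and the SAP is to be validated before the database is frozen.

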## Results

Recruitment started in January 2016. The duration of the inclusion period is 24 months, and the duration of research is 3 years (including 6 months for conducting the study with the last patients included and 6 months for data analysis). The final report will be written based on the CONSORT statement [48] and its adaptation for an eHealth trial [68] (Multimedia Appendix 5).

As of this writing, there have been no major changes during the study (eg, staff turnover, equipment breakdowns). We have lost a subject during the protocol. We are currently making an attrition or engagement diagram of the subjects over time that we will include in the final article once we have the results of the study.

To our knowledge, this is the first French study to examine the effectiveness of a computer-based stress management program (CBT) for patients with ADA.

## Discussion

The aim of this study is to demonstrate the efficacy of 2 therapeutic programs with 120 patients suffering from ADA and to compare these programs. To date, we have 50 of the required 120 participants (42%).

We can already cite as a limitation that because this is an eHealth study, the participants are not blinded to the treatment group.

Some elements of this randomized controlled trial would be different if it were conducted in routine clinical practice. Indeed, currently, patients come to do their eLearning sessions in consultation, so one can easily control adherence, which we would not be able to do if it were in clinical practice. This adherence is reinforced by minimal contact time with a nurse before each session (which is very short).

In clinical practice, a way to assess and reinforce adherence should be found. This issue is why we plan to improve this program by integrating tools from new information and communication technologies (eCBT, mCBT, eCoaching, telemedicine) and rely on a recent literature review concerning adherence to self-help treatment with digital media [37].

We would propose that the program is not just for the psychiatric population (tertiary prevention) but for a wider population exposed to stress who may suffer from stress-related disorders (primary and secondary prevention).

This program would make it easier to access treatment with the aim of preventing stress, which is not available in France at the present time.

